#### Hypersensitivity assessment.

Pain perception in children was evaluated through the Wong-Baker Faces Pain Rating Scale [29] and the Schiff Cold Air Sensitivity Scale (SCASS) [30] will be used for the assessment of the operator and examiner. Following isolation of the neighboring teeth with gauze, compressed air will be applied to the tooth with MIH for three seconds. The SCASS is scored as follows: 0 (no reaction); 1 (no reaction, but patient reports discomfort); 2 (patient reacts and moves away from stimulus); and 3 (patient reacts and asks operator to stop) [3]. Hypersensitivity will be measured using the Wong-Baker Faces Pain Rating Scale and SCASS prior to the procedure, 48 hours after restorative treatment and at four-month intervals for the 12-month follow-up period.

### Statistical analysis

The data will be presented using descriptive statistics. Continuous variables will be described with mean and standard deviation, and categorical variables by relative frequency. Statistical analyses will be conducted using SPSS software (version 28.0, IBM, USA). For comparisons of the Wong-Baker Faces Pain Rating Scale and SCASS scales, a repeated measures analysis of variance (ANOVA) will be used, considering the three groups and five time points of the study. This analysis will address the objective of comparing the effectiveness of interventions in controlling hypersensitivity over time. Post-hoc comparisons will be made using the Bonferroni adjustment to control for Type I error in multiple comparisons. The normality of the data distribution and the homogeneity of variance will be confirmed by the Shapiro-Wilk and Levene tests, respectively. The presence of sphericity will be verified using the Mauchly test, and if violated, corrections such as Greenhouse-Geisser will be applied. For secondary outcomes, repeated measures ANOVA will also be used to compare differences over time among the three intervention groups. Post-hoc analyses with Bonferroni correction will be applied when necessary. Effect sizes (partial eta squared) will be reported to assess the magnitude of differences between interventions. Additionally, Pearson or Spearman correlation coefficients will be used to explore associations between changes in hypersensitivity and secondary outcomes, depending on data distribution. Sensitivity analyses using an intention-to-treat approach may also be performed to assess the robustness of the findings. A significance level of 0.05 will be adopted for all analyses.

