### Objectives

Primary Objective: To determine whether photobiomodulation combined with a new photopolymerizable resin improves hypersensitivity in MIH-affected carious molars.

Secondary objectives:

To compare the effectiveness of three interventions: photobiomodulation combined with self-cure resin, self-cure resin alone, and photobiomodulation combined with bulkfill photopolymerizable resin in controlling hypersensitivity over time.To assess the clinical performance of the self-cure composite resin in terms of restoration longevity.

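### Two hypersensitivity scales are each tested at 0.05 with neither ranked; if either can carry the primary claim, its false-positive rate is up to about 10%

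*Protocol article*

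**What the plan says.** The Objectives section gives the primary aim as "To determine whether photobiomodulation combined with a new photopolymerizable resin improves hypersensitivity in MIH-affected carious molars". It names no scale, visit or contrast.

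The Hypersensitivity assessment section measures this with two instruments, the child's Wong-Baker rating and the SCASS (0 to 3). Both are taken before treatment, at 48 hours, and every four months up to 12 months.

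The Statistical analysis section of the protocol article then states:

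- Method: "For comparisons of the Wong-Baker Faces Pain Rating Scale and SCASS scales", the plan prescribes repeated measures ANOVA. The factors are the three groups and five time points. Scale is not a factor, so this means one ANOVA per scale.
- Purpose: "This analysis will address the objective of comparing the effectiveness of interventions in controlling hypersensitivity over time". This echoes the first secondary objective; no test is explicitly tied to the primary one.
- Multiplicity: "Post-hoc comparisons will be made using the Bonferroni adjustment to control for Type I error in multiple comparisons".
- Other outcomes: "For secondary outcomes, repeated measures ANOVA will also be used to compare differences over time among the three intervention groups". Because these come separately, the two scales appear to share the leading position.
- Level: "A significance level of 0.05 will be adopted for all analyses".

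The Sample size calculation section uses an effect size of 0.352 without saying which scale it refers to, so it does not identify a primary scale either.

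**The concern.** One claim is to be supported by two tests, each at the full 0.05, with no rule linking them. The plan invokes control of Type I error, but its adjustment works inside each ANOVA, among groups and visits. It does not reach the choice between scales.

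Two things are at stake. First, if a positive result on either scale is taken as showing better hypersensitivity, the chance of a false claim exceeds 5%. Second, one scale is the child's own report and the other a scored reaction to cold air, so they can disagree. The text shown gives no way to read a trial that is positive on one and negative on the other, and the choice could then be made after the data are seen.

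**Working it through.** **Inputs.** From the article: 0.05 per test; two scales; three groups of 25; five time points. Assumed, because the article does not give them: correlation between scales, ranged from 0 to 0.9; correlation between visits within a scale, 0.5; normally distributed scores.

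**Step 1: the stated level, one scale and one effect.** Over 40,000 simulated trials per setting with no treatment effect, a single ANOVA effect was significant in 4.9% to 5.1% (group) and 4.9% to 5.2% (group-by-time). The stated 0.05 is reproduced for a single test.

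**Step 2: two scales, one effect each, either one sufficient.**

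- Independent scales: 1 − (1 − 0.05)² = 1 − 0.9025 = 0.0975.
- Upper bound under any correlation: 0.05 + 0.05 = 0.10.

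**Step 3: allow for correlated scales.** Both are read on the same tooth at the same visits, so positive correlation is expected. Simulated chance of at least one significant result:

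| Correlation between scales | Group effect | Group-by-time |
|---|---|---|
| 0 | 9.6% | 9.7% |
| 0.3 | 9.5% | 9.5% |
| 0.5 | 9.3% | 9.1% |
| 0.7 | 8.4% | 8.9% |
| 0.8 | 7.7% | 8.2% |
| 0.9 | 7.2% | 7.3% |

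The simulation standard error near 9.5% is √(0.095 × 0.905 / 40,000) ≈ 0.0015, or 0.15 percentage points. The row at correlation 0 agrees with the exact 9.75%. Relative to 5%, the inflation runs from 7.2/5 ≈ 1.4 to 9.75/5 = 1.95.

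**Step 4: other success rules.**

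- Both scales required: at most 5%, since the joint event cannot be more likely than either test alone.
- One named scale and one named effect: 5%.
- Each scale at 0.025: 1 − (1 − 0.025)² = 0.0494 if independent, and at most 0.025 + 0.025 = 0.05 otherwise. Holm has the same 5% ceiling and is never less powerful.

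**The case against.** **The success rule is inferred.** No sentence says that one positive scale is enough, and requiring both would keep the error at or below 5%. This stands, so the inflation is conditional. It does not remove the point: the text shown contains no both-scales rule either, and the reading that inflates the error is left open.

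**The 0.05 is a per-test level.** This is also right. The article does not promise 5% for the primary claim as a whole. It does cite Type I error control as the reason for its adjustment, and that adjustment stops short of the two scales.

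**The full protocol may settle it.** The article refers to a supporting file with the trial protocol, which is not shown and may rank the scales. The point does not rest on that silence. It rests on what the article fixes: equal treatment of two scales, a uniform level, and an adjustment limited to post-hoc comparisons.

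**Stronger readings that a reader might infer.**

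- That the error is double or more because of the two scales. Two tests at 0.05 cannot exceed 10%, and 9.75% needs independent scales, which is unlikely here.
- That the error reaches 14% to 18%. The simulation gives 14.0% to 18.3% (correlation 0.9 to 0) only if the group effect and the interaction both count on both scales. Most of that excess comes from counting two effects: one scale alone then already gives about 9.7%. The article does not say both count, and its reference to control over time points to the interaction.
- That the four post-treatment visits multiply the tests further. They enter one overall ANOVA, and comparisons after it are Bonferroni-adjusted.

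**The model is simplified.** SCASS is a four-level ordinal score and was simulated as normal. The 9.75% and the 10% bound need only that each test holds its own 5% level; the simulated figures depend on the model.

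**Conclusion.** The point holds in a limited, conditional form. As written, the article leaves two unranked scales, each tested at 0.05, to support one primary objective. If either can carry the claim, the false-positive rate for one ANOVA effect per scale is up to about 10%: 9.75% if independent, and roughly 7% to 9.5% for assumed correlations of 0.9 to 0.3. It is not 5%, and it is not more than double 5%. The conclusion rests on the either-scale reading, which the article neither states nor excludes, and the figures below 9.75% rest on the assumed correlation. The missing rule for a split result does not depend on any of these assumptions. The change is worth making before the data are analysed.

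**What to change.** Keep the planned three-group, five-time-point ANOVA. State that the group-by-time interaction is the deciding effect. Then choose one of:

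1. Name one scale as primary, for example the child's Wong-Baker score, tested at 0.05, with SCASS secondary.
2. Keep both scales and apply Holm: the smaller p-value is tested at 0.025 and, if that succeeds, the larger at 0.05.

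This takes one sentence in the objectives and one in the analysis section. Under option 1, SCASS alone can no longer carry the primary claim. Under option 2 there is a small loss of power, because the smaller p-value must pass 0.025. Either option gives a split result a defined reading.

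Moving the primary test to a single visit would cost more. It would abandon the repeated measures design behind the sample size. A one-visit, three-group ANOVA at the same effect size of 0.352 (noncentrality N × 0.352², 2 and N − 3 degrees of freedom) needs 81 children for 80% power, against the 75 planned.

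If the full protocol already ranks the scales or sets a rule across them, align the article with it.

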### Sample size calculation

The sample size will be estimated using the G*Power software (version 3.1, Franz Faul, Unikiel, Germany) [22] for a priori repeated measures ANOVA. An effect size of 0.352, derived from the group mean dispersions reported in the literature [23], will be considered. The alpha error will be set at 0.05, statistical power at 80%, and the design includes 3 groups and 5 repeated measures. The final calculation indicates the need for 66 individuals in total, corresponding to 22 participants per group. To increase the robustness of the results and compensate for potential dropouts, the sample will be inflated by 15%, resulting in 25 individuals per group and a total of 75 participants.

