### Blinding

All treatments across the three groups will be carried out by a single operator, who will have completed training and calibration sessions during the initial phase of the study. Clinical assessments after 48 hours as well as four, eight and twelve months after treatment (follow-up) will be performed by an examiner blinded to allocation (single-blind study). The operator and examiner will undergo previous calibration exercises, evaluating approximately 20 cases, with the calculation of the Kappa statistic to ensure greater than 85% inter-observer agreement. The calibration will follow the criteria of the modified index of the United States Public Health Service (USPHS) [24,25] and the MIH-SSS diagnostic criteria [20]. The data will be analyzed by a blinded statistician.

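### The hypersensitivity ANOVA uses the pre-treatment reading as one of five outcome time points, without baseline adjustment and without naming the deciding test; this costs power by an amount that rests on unstated assumptions

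*Protocol article*

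**What the plan says.** The Hypersensitivity assessment section schedules the Wong-Baker and SCASS readings "prior to the procedure, 48 hours after restorative treatment and at four-month intervals for the 12-month follow-up period". That is one pre-treatment reading and four post-treatment readings (48 hours, 4, 8 and 12 months).

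The Statistical analysis section then states that for both scales a "repeated measures analysis of variance (ANOVA) will be used, considering the three groups and five time points of the study". It says this addresses the comparison of the interventions over time, with Bonferroni post-hoc comparisons. It names no baseline covariate, change score or mixed model, and does not say whether the group main effect or the group-by-time interaction decides. On assumptions it says: "The normality of the data distribution and the homogeneity of variance will be confirmed by the Shapiro-Wilk and Levene tests, respectively". Intention-to-treat appears only as a sensitivity analysis that may be done.

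The Sample size calculation uses the same five-point layout: "The alpha error will be set at 0.05, statistical power at 80%, and the design includes 3 groups and 5 repeated measures".

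**The concern.** The pre-treatment reading cannot carry a treatment effect. Under randomisation its expected group difference is zero. As one of five outcome levels, it does one of two things:

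- In the group main effect it is averaged in with the other four readings. This shrinks the signal and leaves chance baseline imbalance in the estimate.
- In the group-by-time interaction it serves as one level of a test with (3 − 1) × (5 − 1) = 8 degrees of freedom, which gives no single treatment difference.

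The same reading would usually do more work as a covariate. A real difference between groups could therefore be missed with data able to show it. Because the deciding test is not named, the choice between main effect and interaction could also be made after the results are seen.

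Two further features of the chosen method matter. Classical repeated measures ANOVA in SPSS needs all five readings per child. And SCASS takes only the values 0, 1, 2 and 3, so its normality cannot literally be confirmed.

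**Working it through.** **The plan's own sample size.** Inputs from the Sample size calculation: effect size f = 0.352, alpha 0.05, power 80%, 3 groups, 5 measures. For the between-groups test, λ = f²·N·5/(1 + 4ρ), with 2 and N − 3 degrees of freedom. The correlation ρ is not stated. At ρ = 0.75, N = 66 gives power 0.805, which matches "The final calculation indicates the need for 66 individuals in total, corresponding to 22 participants per group". At ρ = 0.5 the same formula gives N = 51. So 66 is attainable, but the stated inputs do not fix it.

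**Assumptions for the comparison (not in the documents).** Unit SD; N = 66; an effect of 0.6 SD at every post-treatment visit in two of three groups. The group means 0.6, 0.6 and 0 have mean 0.4, so their variance is V = (0.04 + 0.04 + 0.16)/3 = 0.08, and N·V = 5.28. Compound symmetry with correlation ρ.

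**Formulas.** Write the effect profile over the five points as p = (0, 1, 1, 1, 1), with mean 0.8.

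- Five-point group main effect: λ = N·V·0.8² / [(1 + 4ρ)/5], with 2 and 63 df.
- Five-point group-by-time: λ = N·V·Σ(p − 0.8)² / (1 − ρ), where the sum is 0.64 + 4 × 0.04 = 0.8, with 8 and 252 df.
- Mean of the four post-treatment readings with baseline covariate: λ = N·V / [(1 + 3ρ)/4 − ρ²], with 2 and 62 df.

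| ρ | λ main / interaction / adjusted | Power main / interaction / adjusted | λ adjusted ÷ λ main |
|---|---|---|---|
| 0.3 | 7.68 / 6.03 / 13.71 | 0.68 / 0.35 / 0.91 | 1.79 |
| 0.5 | 5.63 / 8.45 / 14.08 | 0.53 / 0.49 / 0.92 | 2.50 |
| 0.7 | 4.45 / 14.08 / 18.53 | 0.44 / 0.75 / 0.97 | 4.17 |

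In each row the first two λ values sum to the third. For a constant effect, the five-point ANOVA splits between two tests the information that the adjusted analysis puts into one.

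**With the plan's f.** If f = 0.352 is taken as the effect at each post-treatment visit (an assumption), power at ρ = 0.5 is 0.74 / 0.71 / 0.99. At ρ = 0.76, close to the value that reproduces 66, it is 0.60 / 0.98 / 1.00.

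**Weaker baseline correlation.** Keep 0.5 among post-treatment readings and take 0.2 with baseline.

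- Main effect: the variance of the five-point mean is (5 + 2 × (6 × 0.5 + 4 × 0.2))/25 = 0.504; λ = 5.28 × 0.64/0.504 = 6.70; power 0.61.
- Adjusted: the residual variance is 0.625 − 0.04 = 0.585; λ = 5.28/0.585 = 9.03; power 0.75.
- Interaction: the average correlation is (6 × 0.5 + 4 × 0.2)/10 = 0.38; λ ≈ 5.28 × 0.8/0.62 = 6.81; power about 0.39. This is approximate because sphericity no longer holds.

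**Waning effect.** Full at 48 hours, half at 4 months, none from 8 months; ρ = 0.5.

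- Main effect: p has mean 0.3; λ = 5.28 × 0.09/0.6 = 0.79; power 0.11.
- Interaction: Σ(p − 0.3)² = 1.25 − 0.45 = 0.8; λ = 8.45; power 0.49.
- Adjusted average: mean 0.375; λ = 5.28 × 0.1406/0.375 = 1.98; power 0.21.
- Joint baseline-adjusted test of group and group-by-visit: λ = 5.28 × (1.25/0.5 − 0.25 × 1.5²/0.75) = 5.28 × 1.75 = 9.24 on 8 df; power about 0.53.

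**Missed visits.** If each post-treatment visit is missed independently by 5% (assumed), 1 − 0.95⁴ = 18.5% of children lack a full record. Of 75 randomised, 75 × 0.815 ≈ 61 remain, fewer than the 66 required.

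**Type I error.** In simulations with no effect and random dropout of 0 to 30%, all the tests rejected in about 4 to 5.5% of runs.

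**The case against.** The strongest reply is that the large gap in power comes from a favourable scenario. It needs a constant effect over 12 months and a baseline correlation as strong as the post-treatment one. Photobiomodulation is given in a single session, so waning is plausible, and then the planned interaction beats the averaged adjusted test (0.49 against 0.21). Hypersensitivity is an entry criterion, which restricts the baseline range and may weaken its correlation with later readings. All of this stands, and it is why the size must be given as a range. It does not rescue the five-point ANOVA: even under waning, the joint baseline-adjusted test (0.53) does not lose to the interaction.

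It is also fair that dilution concerns only the main effect. The wording about comparing effectiveness over time may point to the interaction, which loses little at high correlation (0.98 against 1.00 with f = 0.352 and ρ = 0.76). But the article does not name the interaction as the deciding test, and its sample size is matched by the between-groups calculation at ρ of about 0.75, where the main-effect loss is large.

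A reader might infer that the plan prescribes complete-case analysis. It does not say so. Deletion follows from the usual SPSS procedure and is probable, not stated. The 18.5% rests on an assumed rate and independent misses; clustered misses would cost less. Dropout is also partly provided for: "the sample will be inflated by 15%, resulting in 25 individuals per group and a total of 75 participants".

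A reader might likewise fault the article for giving no fallback if SCASS is not normal. Such detail may sit in the full protocol or analysis plan, which are not shown, so its absence is no finding. What stands is that a normality check is an unsuitable basis for a four-value score.

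**Conclusion.** The point holds as one of efficiency and clarity. The plan fixes a model in which the pre-treatment reading is an outcome level, baseline is not adjusted for, and the deciding test is open. For a constant effect the main effect keeps 0.8 of the signal, and the interaction spends 8 degrees of freedom on it. In the central scenario power is about 53% and 49%, against 92% with baseline adjustment. With baseline correlation 0.2 it is about 61% and 39%, against 75%. With an effect gone by 8 months, the averaged adjusted test falls below the interaction, so the choice of contrast matters as much as the covariate.

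Two stronger readings are not supported. The first is that the trial really has about 50% power: the 0.6 SD effect, the correlations and the constant profile are assumptions, and with the plan's own f the planned tests reach 0.74 and 0.71 at ρ = 0.5. The second is that the planned analysis is invalid: the type I error was sound under random dropout, and randomisation makes chance baseline imbalance a matter of precision. The change should be made, but it is not a fatal flaw.

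**What to change.** Replace the five-point ANOVA for hypersensitivity with a linear mixed model of the four post-treatment readings. Include group, visit, group-by-visit and the baseline score, with unstructured covariance, and use all randomised children who have any post-treatment reading. A constrained longitudinal model, which keeps baseline as a response with a mean common to the groups, is an equally good choice.

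Name the deciding contrast before any unblinded analysis: for example, the adjusted group difference at a stated visit, or averaged over visits, with the joint test of group and group-by-visit in support. If waning is expected, do not rely on the average alone. Report adjusted differences with 95% confidence intervals.

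For SCASS, add a baseline-adjusted ordinal model (proportional-odds mixed model or GEE) in place of reliance on a normality test.

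The cost is analysis wording only. Baseline is already collected, no further child or visit is needed, and SPSS 28 fits these models. One limit remains: the Clinical assessment section removes teeth whose restoration fails. The mixed model does not by itself remove the bias from that outcome-dependent exclusion, which needs separate handling.

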### Randomization

The participants will be randomly allocated to the different groups using block randomization. A computer-generated sequence (random.org; Randomness and Integrity Services, Dublin, Leinster, Ireland) will be used to allocate each participant to a specific group maintaining a 1:1:1 proportion (equal number of participants in all groups). Randomization will be performed in 5 blocks, with 15 participants per block, totaling 75 participants across the study. Allocation concealment will be ensured with the use of sequentially numbered sealed opaque envelopes.

Teeth selected for treatment will be randomized into three groups:

**Group 1**: Photobiomodulation + restoration with self-cure composite resin

**Group 2**: Restoration with self-cure composite resin

**Group 3**: Photobiomodulation + restoration with photopolymerizable bulk-fill composite resin

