#### Group 2 – restoration with self-cure composite resin.

Same as previous sequence (Group 1) with exception of Item 3.

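### The 80% power at 66 children belongs to an omnibus three-group ANOVA; the Group 1 v Group 2 comparison that isolates photobiomodulation is a Bonferroni post-hoc test whose power the plan never considers

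*Protocol article*

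**What the plan says.** All references are to the protocol article.

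- **Sample size calculation.** G*Power was used "for a priori repeated measures ANOVA". The effect size is a single omnibus figure: "An effect size of 0.352, derived from the group mean dispersions reported in the literature". The other inputs are given as "The alpha error will be set at 0.05, statistical power at 80%, and the design includes 3 groups and 5 repeated measures". The result: "The final calculation indicates the need for 66 individuals in total, corresponding to 22 participants per group". After the dropout allowance, "the sample will be inflated by 15%, resulting in 25 individuals per group and a total of 75 participants".
- **Randomization.** Three groups, "maintaining a 1:1:1 proportion (equal number of participants in all groups"): Group 1 has laser plus self-cure resin, Group 2 self-cure resin only, Group 3 laser plus bulk-fill resin.
- **Clinical protocol, Group 2.** "Same as previous sequence (Group 1) with exception of Item 3". Item 3 of the Group 1 sequence is the photobiomodulation step.
- **Statistical analysis.** Repeated measures ANOVA over three groups and five time points is the main analysis. Pairs are handled as follows: "Post-hoc comparisons will be made using the Bonferroni adjustment to control for Type I error in multiple comparisons".

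The article does not state the correlation among the five readings, the ANOVA effect that was powered (group or group-by-time), the assumed pattern of the three means, the number of Bonferroni comparisons, or the power of any pair.

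**The concern.** The primary objective is about whether photobiomodulation, with the new resin, improves hypersensitivity. A significant three-group F does not answer that, because it could come from a resin difference alone. Groups 1 and 3 both receive the laser, and Groups 2 and 3 differ in resin as well as laser. That leaves Group 1 v Group 2 as the one clean contrast, and it is tested at a stricter level than the calculation used.

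Two things are at stake. The trial may show a significant F and no significant pair that isolates the laser. A null Group 1 v Group 2 result may also be read as evidence against photobiomodulation from a trial described as having 80% power, when the chance of detecting the planned effect on that pair was lower.

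**Working it through.** **Inputs from the article:** f = 0.352, alpha 0.05, 3 groups, m = 5 readings, N = 66 or 75, allocation 1:1:1.

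**Assumptions, not in the article:** between-visit correlation ρ; three pairs in the Bonferroni family, so two-sided 0.05/3 = 0.0167; the pattern of means.

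**Step 1. Reproduce 66.** The between-groups F test has

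λ = N f² m / (1 + (m − 1)ρ), with df 2 and N − 3.

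At ρ = 0.75 and N = 66: λ = 66 × 0.1239 × 5 / 4 = 10.22, power 80.5%. At N = 63 it is 78.4%, so 66 is the smallest balanced N. Other correlations give other totals: 51 at ρ = 0.5, 63 at 0.7, 69 at 0.8, 81 at 1.

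This is not the only route. The multivariate (Pillai) group-by-time test, with λ = 2Nf², needs no ρ and gives 80.3% at 65 and 81.1% at 66; balancing 65 gives 22 per group. The univariate interaction returns 66 only at ρ = 0 with sphericity factor 0.25. Each of these is an omnibus test.

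**Step 2. Convert f to a Group 1 v Group 2 difference** (between-groups reading).

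| Pattern of means | d |
|---|---|
| Only the laser matters: Groups 1 and 3 equal, Group 2 differs | 3f/√2 = 0.747 |
| Groups 1 and 2 are the extremes, Group 3 midway (largest gap this f allows) | f√6 = 0.862 |
| Groups 1 and 2 adjacent, means equally spaced | f√6/2 = 0.431 |

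**Step 3. Power of the pair.** Use the five-visit mean, with variance (1 + 4 × 0.75)/5 = 0.8, n per group, df N − 3, and noncentrality (d/√0.8)√(n/2). For the laser-only pattern at n = 22 this is (0.747/0.894) × 3.317 = 2.77, against a critical t of 2.46.

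| Pattern | N = 66 | N = 75 |
|---|---|---|
| Laser only | 62.2% | 69.1% |
| Extremes | 76.7% | 82.8% |
| Adjacent | 20.3% | 23.5% |

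The 76.7% is a ceiling at N = 66 on this reading. The adjacent pattern is not a floor: if Groups 1 and 2 lie closer together, power is lower still.

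**Step 4. The alternative test.** With exactly three groups, a significant omnibus test at 0.05 followed by each pair at an unadjusted 0.05 is a closed testing procedure. Simulation of the laser-only pattern at ρ = 0.75 gives:

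| | N = 66 | N = 75 |
|---|---|---|
| Omnibus | about 80% | about 86% |
| Bonferroni pair | 62% | 69% |
| Omnibus, then unadjusted pair | 73% | 79% |

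The familywise error of the closed procedure is about 5% under the global null. The false-positive rate for Group 1 v Group 3 under the laser-only alternative is also about 5%.

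**Step 5. Limit of that protection.** If the same gate is followed by unadjusted pairs at each of the five visits (N = 66, ρ = 0.75, laser-only), the chance of at least one false Group 1 v Group 3 result is about 13%.

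**The case against.** **62% is one scenario.** A reader might infer that the pair has 62% power on the protocol's own inputs. The article does not support that. The figure needs ρ = 0.75 (solved back from 66), exactly three comparisons, and Group 2 alone differing. This objection stands, so the figure must be given as conditional, with its range.

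**The powered effect is not known.** A reader might infer that the between-groups test is the only one that yields 66. It is not. A laser effect against a shared pre-treatment reading would appear as group-by-time, and the multivariate test of that effect gives 65 to 66. The 62% does not carry over to that reading. Taking f = 0.352 as that routine's effect size with one effect dimension, a Bonferroni Group 1 v Group 2 profile test at N = 66 has roughly 70% power in the laser-only pattern (omnibus 81%) and roughly 85% in the extremes pattern. The mismatch remains for the laser-only case, but the statement that no pattern reaches 80% at 66 belongs to the between-groups reading alone.

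**No primary pair is named.** The primary objective gives no comparator, and the secondary objective is a three-way comparison that an omnibus test suits. Group 1 v Group 2 is inferred from the design. The inference is firm, since no other contrast isolates the laser.

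**Bonferroni is valid.** It controls error and is simply conservative here. The closed procedure protects only the three pairs of one effect; used visit by visit it would fail, as Step 5 shows. This stands and limits the fix.

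**The fix does not reach 80%.** Also true: 73% at 66 and 79% at 75 in the laser-only pattern. Sizing for the Bonferroni pair in that pattern would take 96 children (32 per group) before dropout. It does not follow that the trial must enrol 96, because that figure carries the same unstated assumptions.

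**Conclusion.** The concern holds in a limited form. The 66 children and 80% power are for an omnibus three-group test, whichever ANOVA effect was meant. The comparison needed for a photobiomodulation conclusion is reached only through Bonferroni, and its power is not considered. This is not a detail left to an analysis plan: the article fixes both the sizing basis and the Bonferroni rule, and they do not match.

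The size of the shortfall depends on assumptions. Under the between-groups test, ρ = 0.75 and three pairs, Group 1 v Group 2 has about 62% power at 66 if only the laser matters, and 20% to 77% over the patterns examined. If all 75 are evaluable the figures are 69%, and 24% to 83%. The documents do not support a single definite power for this pair, nor a claim that Bonferroni is an error. They do support saying that the stated 80% should not be read as the power to show a laser effect, and that a less conservative valid test is available for three groups.

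**What to change.** 1. **Statistical analysis section.** For the three between-group comparisons of the single group effect being tested, replace Bonferroni with the closed procedure: the omnibus three-group test of that effect at 0.05, then, only if it is significant, each pair on the same effect at an unadjusted two-sided 0.05. Name the effect (group, or group-by-time). Keep a multiplicity adjustment for any visit-by-visit pairs.
2. **Sample size calculation section.** State that the 80% applies to the omnibus test, and to which effect. Give the Group 1 v Group 2 power under the pairwise test actually used, with the assumed correlation and mean pattern, as a conditional range. On the between-groups reading with ρ = 0.75 and only the laser effective, that is about 62% (Bonferroni) or 73% (closed procedure) at 66, and 69% or 79% at 75. If Bonferroni is kept, this second change is still needed.

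The cost is wording in two paragraphs, with no extra children. The closed procedure does not supply simultaneous confidence intervals, and the stated power for the laser comparison will look less favourable than 80%.
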